## Methods

### Study design

This is an international observational cohort study. The rationale is to evaluate women’s perinatal mental health experiences throughout pregnancy and the first year after childbirth. The general study will extend from 01 December 2022 to 30 June 2023. This date can be changed depending on the situation of the war.

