### Symptoms

Another objective is to evaluate possible risk and protective factors (including social and economic factors, personality traits, social support, and access to medical/mental health services). We are focusing on the two groups of women who were affected by war during pregnancy: those who left Ukraine and are now refugees in other European countries (known as external refugees) and those who chose to remain in Ukraine (in the same place of residence, considered as internal refugees).

The main goals are the following:To evaluate how perinatal mental health has been affected during the war, by observing the differences in (a) levels of depression, anxiety, post-traumatic stress disorder, and birth trauma; as well as in (b) clinical risk indices (proportion of women above the clinical cut-off point on a validated self-report scale)To research which risk and protective factors have a bearing on perinatal mental health during the war.To examine the links between pregnancy results and mental health of women in war-affected areas.To examine the experiences during the birth and delivery, specifically the potential traumatic events during this period.To assess the perinatal women’s needs concerning support and mental health services in Ukraine and in the host countries.

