### Participants

The research sample consists of females in the time around childbirth. To be included in the study at the beginning, participants must meet the following criteria:Being pregnant or a biological mother of an infant up to 12 months of age.Being 18 years or older.Being a war refugee from Ukraine (entrance to EU countries from 24 February 2022) or staying in Ukraine after/during the war.Consenting to take part in the study.

The exclusion criteria are:Not being currently pregnant or not being the biological mother of an infant up to 12 months of age.Younger than 18 years of age.Not consenting to take part in the study.

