### Sample size

No restrictions have been put in place for participant registration. Nevertheless, the sample size was determined by taking into account the number of newborns in Ukraine. Consequently, a minimum sample size of 300 individuals will be recruited using a significance level of α-level of 0.05 and variability of 50%. It is essential to bear in mind, though, that the ongoing war situation, which includes the lack of electricity in Ukraine, the possibility of people evacuating cities, and missiles, may make it challenging to reach this sample size.

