### Assessment, care, and trust—In pregnant and new mothers

This questionnaire includes 40 questions to record sociodemographic data, including current residence, education, number of prior pregnancies, the number of biological children (including miscarriages), the number of individuals residing in their home (adults and children), marital status, whether they are living with a partner, basic information concerning the location after the war outbreak and access to support, changes since the beginning of the war, exposure to armed-conflict or limitations to medical support and social support. This questionnaire was created for this study.

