### Impact of events scale-revised

The Impact of Event Scale-Revised (IES-R; Weiss and Marmar, 1997) is a self-assessment tool measure for capturing the level of symptomatic response to specific traumatic stressors as it was manifested in the previous 7 days.

The scale has been translated into different languages (Baguena et al., 2001; Asukai et al., 2002) and different samples (Beck et al., 2008) with good psychometric properties.

A revised version of the Impact of Event Scale-Revised by Weiss and Marmar (1997), contains 22 items with scores gathered using a 5-point scale (0–4). What differentiates this revised version of the Impact of Event Scale (IES-R) from the previous one is that this latest version has seven additional questions and a scoring range of 0 to 88.

On this test, a score of 24 or more is clinically significant as it is indicative of an individual having full or partial PTSD. A score of 33 or more is the most accurate way to determine the probability of PTSD, and a score of 37 or higher is a strong indication of the disorder (Weiss, 2007).

This questionnaire considers the three dimensions of PTSD according to DSM-IV (Weiss and Marmar, 1997), including the following: Intruding recurring images, dreams, and/or thoughts or perceptual impressions related to the traumatic event; Agitation characterized by increased alertness, anxiety, impatience, and/or difficulty concentrating attention; and Avoidance manifested by efforts to get rid of thoughts, emotions, or conversations related to the traumatic event.

The Ukrainian version “Шкала впливу стресових подій – переглянута (ШВСП-П)” was translated into Ukrainian by the study authors.

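### The date of response is used in no listed variable, test or model, although the study window may move with the war, so calendar time is a potential, unaddressed confounder of the Ukraine-abroad comparison

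*Protocol article*

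**What the plan says.** All references are to the protocol article.

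- **Study design.** "The general study will extend from 01 December 2022 to 30 June 2023", followed by "This date can be changed depending on the situation of the war". No rule for such a change is given.
- **Setting and Procedure.** There is one online questionnaire, reached through one project website.
- **Sample size.** The minimum is 300 women. A caveat is added: "the ongoing war situation, which includes the lack of electricity in Ukraine, the possibility of people evacuating cities, and missiles, may make it challenging". It concerns attaining that number.
- **Aims (under the heading Symptoms).** The two groups of interest are "those who left Ukraine and are now refugees in other European countries (known as external refugees) and those who chose to remain in Ukraine". The first goal is pursued "by observing the differences in (a) levels of depression, anxiety, post-traumatic stress disorder, and birth trauma", and in the proportions above clinical cut-offs. The goal does not name the groups between which differences are taken.
- **Impact of events scale-revised.** Symptoms are rated "as it was manifested in the previous 7 days".
- **Table 1 and the ACT-PNM description.** War exposure is a predictor. The study's own 40-item questionnaire is summarised as covering, among other things, "basic information concerning the location after the war outbreak and access to support, changes since the beginning of the war, exposure to armed-conflict". Neither place names a survey date or calendar time.
- **Data analysis.** Comparisons are by Pearson's chi-square and Student's t, without adjustment. The prediction models start from all the predictors already described and drop variables by p-value. A forward stepwise logistic regression is also planned.

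**The concern.** Three features of the plan act together. The window can move with the war, which is the exposure under study. The named obstacles are war conditions, with the loss of electricity placed explicitly in Ukraine, and the survey can only be answered online. At least one outcome reflects the week in which the woman answers.

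If women in Ukraine and women abroad answer at different times, and symptoms change over those months, a crude comparison of the two groups mixes location with timing. The plan considers the war's effect on how many women respond, but not on when they respond. Its analysis has no term that could separate the two. The results are meant to inform policymakers about needs in Ukraine and in host countries, so a timing difference read as a location difference would mislead.

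**Working it through.** **1. Is a date of response used anywhere?**

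| Place in the article | Content related to time | Date of response? |
|---|---|---|
| Table 1, predictors | War exposure, access to services, pregnancy outcome and others | No |
| ACT-PNM description | Location after the outbreak, changes since the war began, conflict exposure | Not named (items summarised only) |
| Data analysis, Descriptive | Unadjusted chi-square and t tests | No |
| Data analysis, prediction models | All predictors already described, then p-value elimination | No |
| Data analysis, logistic regression | Forward selection | No |

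The model predictors are defined by reference to the described variables, so the plan as written contains no calendar term. If one were added, p-value selection could remove it.

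**2. When does this produce bias?**

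Split the window into two periods with proportions above a cut-off p1 and p2, the same in both groups, so that there is no true group difference. Let s be the share of a group answering in period 1.

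- Group rate = s × p1 + (1 − s) × p2
- Spurious difference = (s abroad − s Ukraine) × (p1 − p2)

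The difference is a product. It is zero if the timing is equal or if symptoms do not change.

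**3. How large could it be?**

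From the document: 300 women in all, alpha 0.05 (taken as two-sided). Assumed, because the document gives no values: an even split of 150 per group, p1 and p2, and the timing shares.

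- SE = √{[pU(1 − pU) + pA(1 − pA)] / 150}
- Rejection probability = P(|Z + difference/SE| > 1.96)

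Worked case: p1 = 0.40, p2 = 0.30, with 30% of women in Ukraine and 70% of women abroad answering in period 1.

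- Ukraine: 0.3 × 0.40 + 0.7 × 0.30 = 0.33
- Abroad: 0.7 × 0.40 + 0.3 × 0.30 = 0.37
- Difference = 0.04; SE = √[(0.2211 + 0.2331)/150] = 0.055; ratio = 0.73; rejection probability = 0.112

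| p1, p2 | Shares in period 1 (Ukraine/abroad) | Spurious difference, points | Odds ratio, Ukraine v abroad | False-positive rate |
|---|---|---|---|---|
| any of the three below | 50/50 | 0 | 1.00 | 5% |
| 35%, 30% | 40/60 to 20/80 | 1 to 3 | 0.96 to 0.87 | 5.4% to 8.6% |
| 40%, 30% | 40/60 to 20/80 | 2 to 6 | 0.92 to 0.77 | 6.5% to 19% |
| 45%, 25% | 40/60 to 20/80 | 4 to 12 | 0.84 to 0.59 | 11% to 59% |

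With the timing shares reversed, the sign reverses.

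**4. Can rates be shown by group and month?**

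Seven months and 150 women per group give 150/7 ≈ 21 women per cell. At a rate of 35% the 95% half-width is 1.96 × √(0.35 × 0.65/21) ≈ 0.20, or 20 points. The distribution of response dates by group is informative at this sample size; monthly rates are not.

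**The case against.** The strongest case against is that the article is condensed, that a movable end date in wartime is an openly stated contingency, and that adjustment for calendar time is commonly left to a full plan. The 40 questionnaire items are not listed, and an online platform would normally stamp each entry. War exposure is already a predictor. The sample size section speaks of numbers recruited, not of timing by group, and a power cut may delay a 35-minute questionnaire by hours rather than months.

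Much of this stands. It is likely that a completion date will exist, so the point is limited to its use. What does not stand is that the matter is simply left open: the article describes unadjusted tests and ties the model predictors to a list without a calendar term.

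A reader might also infer stronger things that the documents do not support:

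- **That the group difference is in fact mixed with timing.** This needs both unequal response dates and a change in symptoms over the window. Neither is stated.
- **That women in Ukraine answer in calmer weeks.** This is plausible from the named obstacles, but it is an inference, and the direction could differ.
- **That the date could move for one group only, or in view of the symptom data.** The sentence concerns the study as a whole, and there is one questionnaire link for all.
- **That the sample will include post-war women.** The criterion "staying in Ukraine after/during the war" can equally mean after the outbreak.
- **That calendar time is purely a confounder of war exposure.** Current war intensity is part of that exposure, so adjustment could remove some of the effect of interest.

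The illustration also assumes that symptoms abroad follow the same course as in Ukraine. If they do not, a shared calendar term removes only part of the problem. Nor does it correct selection by week or by locality within Ukraine.

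**Conclusion.** The point holds in conditional form. Calendar time of response is a potential confounder of the Ukraine-abroad comparison that the plan does not address, most clearly for the IES-R because of its 7-day recall.

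Its size cannot be derived from the documents. On the assumed inputs it ranges from nothing, when response dates are equal in the two groups, to 12 percentage points and a false-positive rate of about 59%. The upper end needs both a 20-point change in the proportion above the cut-off and an 80/20 split in timing; the middle scenario gives 2 to 6 points. These figures rest on 150 women per group, a two-period split and the same symptom course in both groups.

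This is an inexpensive improvement to the analysis. It does not show that the study's results will be biased.

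**What to change.** 1. Keep the completion date of each questionnaire as an analysis variable.
2. Report the distribution of response dates for women in Ukraine and women abroad. If the two distributions are alike, confounding of this comparison by calendar time is small.
3. In the Ukraine-abroad comparisons, include calendar time as a smooth term or as month, and exempt it from p-value elimination and forward selection. The unadjusted chi-square and t results can stay beside the adjusted ones.
4. Show war-exposure estimates with and without the calendar term, and do not treat the adjusted one alone as the answer.
5. State that any change to the end date applies to both groups and is decided without sight of the symptom data.

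The cost is one or two degrees of freedom for a smooth term, or up to six for seven months, with slightly wider intervals. If the platform stores entry times, which is likely but not stated, no further data collection is needed.

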### Setting

The study will be based online on https://blogs.uned.es/mama/ and carried out in European countries which host war refugees and in Ukraine.

### Participants

The research sample consists of females in the time around childbirth. To be included in the study at the beginning, participants must meet the following criteria:Being pregnant or a biological mother of an infant up to 12 months of age.Being 18 years or older.Being a war refugee from Ukraine (entrance to EU countries from 24 February 2022) or staying in Ukraine after/during the war.Consenting to take part in the study.

The exclusion criteria are:Not being currently pregnant or not being the biological mother of an infant up to 12 months of age.Younger than 18 years of age.Not consenting to take part in the study.

### Sample size

No restrictions have been put in place for participant registration. Nevertheless, the sample size was determined by taking into account the number of newborns in Ukraine. Consequently, a minimum sample size of 300 individuals will be recruited using a significance level of α-level of 0.05 and variability of 50%. It is essential to bear in mind, though, that the ongoing war situation, which includes the lack of electricity in Ukraine, the possibility of people evacuating cities, and missiles, may make it challenging to reach this sample size.

### Variables and measures

An overview of the assessment measures is provided in Table 1.

**Table 1 tab1:** Variables and measures used in the study.

Variables	Measures	References
**Independent/predictor**		
Social support	ACT-PNM	NA
Coping strategies	ACT-PNM	NA
Emotional impact	ACT-PNM	NA
War exposure	ACT-PNM	NA
Pregnancy outcome (birthweight, preterm birth, complications?)	ACT-PNM	NA
Health background/ earlier mental health, substance use,	ACT-PNM	NA
access to the perinatal health services	ACT-PNM	NA
Pregnancy outcome (birthweight, preterm birth, complications?)	ACT-PNM	NA
**Dependent/outcomes**		
Depression symptoms	EPDS	Cox et al. (1987)
Anxiety symptoms	GAD-7	Spitzer et al. (2006)
PTSD symptoms	IES-R	Weiss and Marmar (1997)
Birth PTSD	City BiTS	Ayers et al. (2018)
Personality	The 10-item personality inventory (TIPI)	Gosling et al. (2003)

NA = Not Applicable.

### Assessment, care, and trust—In pregnant and new mothers

This questionnaire includes 40 questions to record sociodemographic data, including current residence, education, number of prior pregnancies, the number of biological children (including miscarriages), the number of individuals residing in their home (adults and children), marital status, whether they are living with a partner, basic information concerning the location after the war outbreak and access to support, changes since the beginning of the war, exposure to armed-conflict or limitations to medical support and social support. This questionnaire was created for this study.

### Edinburgh postnatal depression scale

The Edinburgh Postnatal Depression Scale (EPDS; Cox et al., 1987) is the most widely used self-assessment tool designed to recognized women at risk for perinatal depression (Hahn-Holbrook et al., 2017 < NICE. National Institute for Health and Care Excellence, 2017). This scale includes 10 items measuring common symptoms of depression and anxiety. The scores range from 0 to 30. The cut-off values of 10 or higher and 13 or higher are most often used to identify women who are at risk for depression (Levis et al., 2020). However, 13 has been shown to be the most useful cut-off point established in previous studies. The positive predictive value of EPDS is estimated to be 70% (Cox et al., 1987) or even 90% (Levis et al., 2020). A systematic review has also shown that the EPDS has good psychometric properties in low and middle countries (Shrestha et al., 2016). The EPDS has been validated in over 60 languages (Cox et al., 1987; Gibson et al., 2009; Cox, 2019; Vázquez and Míguez, 2019; Levis et al., 2020). The Ukrainian version, “Единбурзька шкала післяпологової депресії (ЕШПД)” was translated by the study authors.

### Generalized anxiety disorder screener, GAD-7

The GAD-7 (Spitzer et al., 2006) is a 7-item instrument that assesses each of the seven symptoms of general anxiety disorder. The GAD-7 screens for anxiety symptoms in the general population and according to the criteria established by the Diagnostic and Statistical Manual of Mental Disorders (DSM)-IV and DSM-IV-TR (American Psychiatric Association, 1994; American Psychiatric Association, 2000). The GAD-7 total score ranges from 0 to 21. The scale’s total score indicates the level of anxiety symptoms, with higher scores reflecting a greater anxiety severity. Scores of 5, 10, and 15 represent cut-off points for mild, moderate and severe anxiety, respectively (Spitzer et al., 2006). When screening for an anxiety disorder, a recommended cut-off point for referral for further evaluation is 10 or greater (Spitzer et al., 2006). The Ukrainian version of the GAD-7 is available (Romanchuk, 2011) but no psychometric properties have been studied yet. The GAD-7 has shown good psychometric properties during pregnancy (Soto-Balbuena et al., 2021) and the postpartum period (Simpson et al., 2014; Fairbrother et al., 2019).

### Experience during the birth: City BIRTH

The City Birth Questionnaire (Ayers et al., 2018) evaluates PTSD symptoms within the context of childbirth and it contains 29 items related to the DSM-5 diagnostic criteria. It also has two other remaining questions related to the DSM-IV diagnostic criteria. This questionnaire examines participant’s subjective feelings of discomfort related to a specific traumatic event. The City Birth Trauma Scale assesses two factors, Birth-related symptoms and General symptoms of re-experiencing the traumatic event (Ayers et al., 2018; Nakić Radoš et al., 2020). The scores range from 0 to 60. As the authors have pointed out, the scores for percentiles are 25th = 3, 50th = 9, 75th = 18. The questionnaire has shown good psychometric properties (Ayers et al., 2018; Nakić Radoš et al., 2020).

The Ukrainian version, “Міська шкала пологової травми” was translated for the purpose of the study by the authors.

### Impact of events scale-revised

The Impact of Event Scale-Revised (IES-R; Weiss and Marmar, 1997) is a self-assessment tool measure for capturing the level of symptomatic response to specific traumatic stressors as it was manifested in the previous 7 days.

The scale has been translated into different languages (Baguena et al., 2001; Asukai et al., 2002) and different samples (Beck et al., 2008) with good psychometric properties.

A revised version of the Impact of Event Scale-Revised by Weiss and Marmar (1997), contains 22 items with scores gathered using a 5-point scale (0–4). What differentiates this revised version of the Impact of Event Scale (IES-R) from the previous one is that this latest version has seven additional questions and a scoring range of 0 to 88.

On this test, a score of 24 or more is clinically significant as it is indicative of an individual having full or partial PTSD. A score of 33 or more is the most accurate way to determine the probability of PTSD, and a score of 37 or higher is a strong indication of the disorder (Weiss, 2007).

This questionnaire considers the three dimensions of PTSD according to DSM-IV (Weiss and Marmar, 1997), including the following: Intruding recurring images, dreams, and/or thoughts or perceptual impressions related to the traumatic event; Agitation characterized by increased alertness, anxiety, impatience, and/or difficulty concentrating attention; and Avoidance manifested by efforts to get rid of thoughts, emotions, or conversations related to the traumatic event.

The Ukrainian version “Шкала впливу стресових подій – переглянута (ШВСП-П)” was translated into Ukrainian by the study authors.

### Ten-item personality inventory

The Ten-Item Personality Inventory (TIPI; Gosling et al., 2003) measures the “Big Five” traits of personality, including neuroticism, extraversion, conscientiousness, openness to experience, and agreeableness (Costa and McCrae, 1992). Research shows that this two-minute questionnaire is a relatively accurate and reliable tool for measuring personality (Sosnowska et al., 2020). In each of the 5 subscales, scores range from 2 to 14 (two points on each subscale; the scores range for each point is from 1 to 7) TIPI scale scoring (“R” denotes reverse-scored items): Extraversion: 1, 6R; Agreeableness: 2R, 7; Conscientiousness; 3, 8R; Emotional Stability: 4R, 9; Openness to Experiences: 5, 10R (Gosling et al., 2003). This questionnaire has a Ukranian adaptation (Klimanska and Haletska, 2019).

### Translations of the measures

Three instruments were translated to Ukrainian in this study. The Edinburgh Postnatal Depression Scale (Cox et al., 1987) was translated by [name], [name], and [name] The City Birth Trauma Scale (Ayers et al., 2018) was translated by [name], [name], [name], and [name] The impact of events scale-revised (Weiss and Marmar’s, 1997) was translated by [name], [name], and [name] The translation was carried out according to Brislin’s translation model (Brislin, 1970; 1986), applicable to the preparation of instruments for cross-cultural research. The back translations were carried out, and the detailed procedure of the translations is available from the authors.

